### Retention

We will continuously monitor the trial for any operational issues (e.g., failure in appointment management, IT-issues). We will communicate timely and directly with the enrolled general practices. As regards data collection of quantitative and qualitative data, data will be provided by participants who are remunerated, thereby increasing the availability of data. We will reduce participant burden by using an electronic survey and keeping questionnaires as short as possible. To encourage retention at point of data collection, we will send out up to three reminders via e-mail and phone.

### Blinding

Given the nature of this real-life intervention, general practitioners and endocrinologists cannot be blinded to their allocation to either the intervention or comparison arm. To limit influencing the behaviour of the control group, baseline information will not be collected from them and are not informed about the type of data that are collected for the main analysis at month 12. Researchers analysing the data will be blinded regarding which arm each general practice belongs to.

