### Data collection

Table 3 shows the study schedule including data collection points according to the SPIRIT guideline. Data are collected at month 0, 12, and 24 for the intervention group and month 12 and 24 for the control group.

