#### Clinical outcomes

Clinical outcomes will be collected from an IT-platform (DEN: “Diabetes Overblik”. ENG: “Diabetes Overview”) used by Danish general practices, which contains anonymous and aggregated diabetes data about patients (Additional file 3 shows screenshots). As per the agreement to participate in the study, each general practice assigns a contact person who will e-mail the screenshot of the data to the project group. Each general practice is renumerated for performing this activity. Data will also be obtained from nationwide Danish registries: The Clinical Laboratory Information System Research Database (LABKA), The Danish National Prescription Registry (DNPR), The Danish National Health Service Register (NHSR), The Danish Civil Registration System (CRS), and The Danish National Patient Register (NPR). Register data will be linked to the unique provider number of each general practice.

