#### Difference between intervention and control group

The main analysis concerns the difference between the intervention and control group at month 12. Data from the Diabetes Overview and general practice survey are analysed using simple, multiple, and logistic regression analyses. Analysis is done according to the intention-to-treat principle to test if the groups differ in terms of outcome measures. The analysis of survey data will take into account cluster effects using the intra-cluster correlation coefficient. Using *t*-test and *Χ*^2^ tests, depending on the outcome measure, it will be determined if randomization has resulted in systematically different groups. Survey data are tested to determine if questions or indices of questions are internally consistent (Cronbach alpha). In the regression analyses, control variables at the individual (e.g., seniority) and practice level (e.g., form and size of practice) are tested to determine its influence on survey outcomes.

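### The month-12 comparison cannot adjust for a practice's starting level because controls supply no month-0 data, although registers already planned could give a baseline for both arms without contacting controls

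*Protocol article*

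**What the plan says.** All references are to the protocol article.

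- **Schedule (Data collection):** "Data are collected at month 0, 12, and 24 for the intervention group and month 12 and 24 for the control group".
- **Reason (Blinding, repeated in the Discussion):** for controls, "baseline information will not be collected from them", in order to limit any influence on what they do.
- **Main comparison (Difference between intervention and control group):** "The main analysis concerns the difference between the intervention and control group at month 12". The data and models are given as follows: "Data from the Diabetes Overview and general practice survey are analysed using simple, multiple, and logistic regression analyses".
- **Covariates (same section):** individual and practice characteristics such as seniority and the form and size of the practice "are tested to determine its influence on survey outcomes". No covariate is named for the clinical outcomes.
- **Registers (Data collection, Clinical outcomes):** "Data will also be obtained from nationwide Danish registries", namely the laboratory, prescription, health service, civil registration and patient registers. "Register data will be linked to the unique provider number of each general practice". No arm and no period is excluded, and the main analysis gives the registers no stated role.
- **Comparability (Difference between intervention and control group):** using t and chi-square tests, "it will be determined if randomization has resulted in systematically different groups". The variables are not named.

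**The concern.** Randomisation is by practice and about 30 practices are expected. With 15 per arm, the arms can differ noticeably by chance in how many eligible patients were already on the recommended drugs. A practice that prescribed more at the start is likely to prescribe more at month 12, whatever its allocation. Adjusting for the starting level removes that part of the variation. On the stated schedule this cannot be done from the Diabetes Overview, because only the intervention arm has a month-0 value.

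The reason given is a good one for not asking controls for screenshots or survey answers. It does not apply to data that reach the project through a provider number without the practice doing anything. Prescriptions, albuminuria and LDL results, and diagnoses of heart disease or stroke are what define the three primary outcomes, and these are the kinds of data that the named registers hold. The power section says that Danish register data already fed the power calculation for these outcomes.

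The number of practices is limited by circumstance (100 in the municipality, 30 expected), so it cannot easily be raised to gain precision.

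**Working it through.** **Inputs from the article:** 15 practices per arm; threshold 0.05/3 = 0.0167 per primary outcome, two-sided; stated power 0.8870, 0.9941 and 0.9848 for outcomes 1, 2 and 3.

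**Assumed, not in the article:** the practice-level correlation r between the pre-randomisation value and the month-12 value, taken as 0.3, 0.5 and 0.7.

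**What can be reproduced:** the threshold 0.0167 can. The stated powers cannot, because their inputs are in Additional file 5, which is not at hand. It is also unknown whether they were computed at 0.05 or at 0.0167, so both cases are carried.

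**Step 1: chance imbalance.** In units of the between-practice SD, the baseline difference between arms has SD √(2/15) = 0.365, with a 95% range of ±1.96 × 0.365 = ±0.72. The probability that it exceeds 0.5 SD in either direction is 2 × [1 − Φ(0.5/0.365)] = 0.17.

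**Step 2: what an imbalance does.** A baseline difference b shifts the unadjusted month-12 difference by r × b. For b = 0.5 SD that is 0.15, 0.25 or 0.35 SD for r = 0.3, 0.5 or 0.7. Given b, the unadjusted test statistic under no effect has mean r·b/0.365 and SD √(1 − r²). Against the critical value 2.394, the conditional type I error is:

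| b (SD) | r = 0.3 | r = 0.5 | r = 0.7 |
|---|---|---|---|
| 0.365 | 0.016 | 0.015 | 0.009 |
| 0.5 | 0.021 | 0.024 | 0.022 |
| 0.716 | 0.030 | 0.051 | 0.076 |

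It lies below 0.0167 for small imbalances and above it for large ones. Averaged over randomisation it is nominal.

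**Step 3: precision.** Adjustment multiplies the variance of the arm difference by 1 − r². The equivalent number of practices per arm is 15/(1 − r²) = 16.5, 20.0 and 29.4, that is 1.10, 1.33 and 1.96 times as many.

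**Step 4: power at 0.0167.** The noncentrality implied by a stated power P is z(P) + z(1 − α/2). For outcome 1 it is 1.211 + 1.960 = 3.171 if α was 0.05, and 1.211 + 2.394 = 3.605 if α was 0.0167. Adjusted power = Φ(noncentrality/√(1 − r²) − 2.394).

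| Outcome, α behind the stated power | Unadjusted | r = 0.3 | r = 0.5 | r = 0.7 |
|---|---|---|---|---|
| 1, 0.0167 | 0.887 | 0.917 | 0.962 | 0.996 |
| 1, 0.05 | 0.781 | 0.824 | 0.897 | 0.980 |
| 2, 0.0167 | 0.994 | 0.997 | >0.999 | >0.999 |
| 2, 0.05 | 0.981 | 0.989 | 0.997 | >0.999 |
| 3, 0.0167 | 0.985 | 0.992 | 0.998 | >0.999 |
| 3, 0.05 | 0.958 | 0.973 | 0.991 | >0.999 |

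Repeating this for outcome 1 with t distributions (28 df unadjusted, 27 df adjusted) gives 0.887 rising to 0.916, 0.961 and 0.996, or 0.765 rising to 0.807, 0.884 and 0.975. The lost degree of freedom hardly matters.

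**The case against.** **The article never says that there will be no baseline adjustment.** It says that controls will not be asked for baseline data. A register baseline is not excluded, multiple regression is planned, and a covariate list is often left to an analysis plan. This stands in part: the absence of adjustment is inferred from the schedule, the named data source and the named covariates. But the schedule and the source are fixed in the article, and on them the adjustment is impossible. Only the registers could supply it, and they have no stated role in the main analysis.

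**Randomisation is already stratified.** This is true: it uses number of full-time GPs and geographic location. A reader might infer that the trial has no other protection against imbalance, and that would be wrong. Neither factor is the starting level of prescribing, so some chance difference remains.

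**Validity is not at stake.** This is correct. The test already allows for chance imbalance, and overall type I error is nominal. What is lost is precision and protection against conditional bias.

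**The size depends on an unknown r.** This is also correct. At r = 0.3, outcome 1 gains only 3 to 4 percentage points of power, and outcomes 2 and 3 have little to gain at any r. Nothing in the article shows that starting level is the main source of variation or that adjustment is the largest gain available.

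**Register and Diabetes Overview definitions may differ.** The Overview depends on coding and list review in each practice, and the extract period is not stated. A covariate need only correlate with the outcome, not match it, but a mismatch would lower r.

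**The comparability tests.** A reader might infer that the planned t and chi-square tests would be run on month-12 outcomes, because controls have nothing earlier. The article does not say which variables are tested. Practice size, location and seniority are available without a baseline request, so that inference is not supported.

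**Conclusion.** The point holds as a matter of efficiency and conditional bias. On the stated schedule, the primary outcomes cannot be adjusted for a practice's starting level from the source analysed, and the reason for leaving controls without a baseline does not reach the registers already planned.

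The benefit lies mainly in outcome 1, with 3 to 20 percentage points of power for r between 0.3 and 0.7, depending also on the α behind the stated power. For outcomes 2 and 3 it is at most about 4 points. A baseline covariate would also limit the effect of a chance imbalance such as the 0.5 SD difference that 17% of allocations would exceed.

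These figures rest on an assumed r, on a practice-level normal approximation with 15 practices per arm, and on the registers reaching back before randomisation. That last assumption is reasonable, given their use in the power calculation, but it is not stated. The change should be made, although the trial would remain valid without it.

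**What to change.** - For both arms, extract from the laboratory, prescription and patient registers each practice's value of the three primary outcomes in one fixed window before randomisation. Controls still receive no baseline request.
- Prespecify each value as a practice-level covariate in the month-12 model for the corresponding outcome.
- Report the values by arm in a descriptive baseline table, and state which variables the planned comparability check uses.
- State the period of the register extract, and how the register definitions relate to those in the Diabetes Overview.

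The cost is more than wording. Three register-based outcome definitions have to be built per practice, the extract has to reach further back, and each model loses one degree of freedom. The gain shrinks if the two sources define patients or treatment differently. The covariate would also not correct for a change in the Diabetes Overview denominator after practices review their diabetes lists as part of the intervention.

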### Data collection

Table 3 shows the study schedule including data collection points according to the SPIRIT guideline. Data are collected at month 0, 12, and 24 for the intervention group and month 12 and 24 for the control group.

**Table 3 Tab3:**
[figure not shown]
Study schedule

#### Clinical outcomes

Clinical outcomes will be collected from an IT-platform (DEN: “Diabetes Overblik”. ENG: “Diabetes Overview”) used by Danish general practices, which contains anonymous and aggregated diabetes data about patients (Additional file 3 shows screenshots). As per the agreement to participate in the study, each general practice assigns a contact person who will e-mail the screenshot of the data to the project group. Each general practice is renumerated for performing this activity. Data will also be obtained from nationwide Danish registries: The Clinical Laboratory Information System Research Database (LABKA), The Danish National Prescription Registry (DNPR), The Danish National Health Service Register (NHSR), The Danish Civil Registration System (CRS), and The Danish National Patient Register (NPR). Register data will be linked to the unique provider number of each general practice.

#### Competence and organization outcomes

Diabetes competence and organization outcomes in general practice will be collected using an electronic survey (Additional file 4) that was developed with inspiration from a survey similarly concerned with diabetes competence and confidence [37]. The main part of the survey asks respondents about their degree of confidence in managing T2D along seven themes: T2D care in general, T2D care and skills in general, T2D care and cardiovascular disease, T2D care and heart failure, T2D care and blood pressure, T2D care and kidney disease, and T2D care and cholesterol. Other questions concern the respondent, the general practice, organization of diabetes care in the general practice, respondents’ assessment of the virtual specialist conferences via Technology Acceptance Model [38, 39], and collaboration using relational coordination [40]. Answers are given on 1–5 Likert scale. The questionnaire is pilot tested for face validity by GPs.

### Sample and power calculation

The pragmatic nature of the RCT means that the sample size is determined by two contextual circumstances: a formal agreement with PLO-Aarhus and PLO-M to run the study in Aarhus Municipality (cf. above) where the total population of general practices was 100 and the fact that Danish general practices operate as private firms and thus decide themselves if they want to participate in a project. Based on these circumstances along with the study team’s research experiences with recruiting general practices, we used opinion-seeking to derive at the number of 30 general practices that were expected to participate.

We calculated the power for finding a significant difference between the intervention and control group on the three primary clinical outcomes using data from Danish registries and opinion-seeking within the study team. Additional file 5 shows the key parameters and the STATA command we used to calculate the following three power values:Power of 0.8870 for Primary clinical outcome 1: Percentage of patients with T2D and ischemic heart disease and/or stroke being treated with GLP1-RA and SGLT2 inhibitorPower of 0.9941 for Primary clinical outcome 2: Percentage of patients with micro/macro-albuminuria being treated with ACE or AT2Power of 0.9848 for Primary clinical outcome 3: Percentage of patients with LDL > 2.5 mmol/L being treated with Statins.

### Statistical analysis plan

Statistical significance is expressed in 95% two-sided confidence intervals. A *p*-value of < 0.05 will indicate statistical significance.

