### Outcomes

#### Clinical outcomes

Table 2 shows the primary and secondary patient outcome measures. The primary patient outcomes are the percentage of patients with T2D and three types of co-morbidities on appropriate diabetes-related medication: ischemic heart disease and/or stroke; micro- or macro-albuminuria; and LDL > 2.5 mmol/L. To account for multiplicity, we use the Bonferroni correction method to adjust the *p*-values of the three primary clinical outcomes. The Bonferroni correction sets the significance cut-off at α/n [36], which means we only reject the null hypothesis of a primary clinical outcome if the *p*-value is less than 0.0167 (i.e., 0.05/3).

**Table 2 Tab2:** Overview of primary and secondary outcomes measures

Aspect	Outcome measure
Primary clinical outcome measures	Percentage of patients with T2D and ischemic heart disease and/or stroke being treated with glucagon-like peptide 1 receptor agonists (GLP1-RA) and sodium glucose cotransporter 2 (SGLT2) inhibitor
	Percentage of patients with T2D and micro/macro-albuminuria being treated with angiotensin-converting-enzyme-inhibitor (ACE) or angiotensin-2-receptorantagonist (AT2)
	Percentage of patients with T2D and LDL > 2.5 mmol/L being treated with statins
Secondary clinical outcome measures	Percentage of patients with T2D and HbA1c < 58 mmol/L
	Percentage of patients with T2D and HbA1c < 53 mmol/L
	Percentage of patients with T2D and blood pressure < 140 mmHg
	Percentage of patients with T2D and blood pressure < 130 mmHg
	Percentage of patients with T2D and low-density lipoprotein > 2.5 mmol/L
	Percentage of patients with T2D and microalbuminuria and LDL > 1.8 mmol/L
Primary competence and organization outcome measures	The extent to which the GP is confident managing T2D in general
	The extent to which the GP is skilled in making decisions on T2D in general
	The extent to which the GP is confident managing T2D and ischemic heart disease, stroke, peripheral artery disease, and heart failure
	The extent to which the GP is confident managing T2D and blood pressure
	The extent to which the GP is confident managing T2D and kidney disease
	The extent to which the GP is confident managing T2D and cholesterol
Secondary competence and organization outcome measures	GPs rating of the degree of relational coordination within the general practice
	GPs rating of the degree of relational coordination with the endocrinology department

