#### Competence and organization outcomes

Table 2 shows the primary and secondary outcome measures at the general practice level. The primary outcome concerns the competence of the GPs with regards to managing T2D and their patient population living with T2D. The secondary outcome measures are (a) the competence of the practice staff with regards to co-managing patients with T2D and (b) GPs and practice staffs’ rating of the degree of relational coordination within the general practice, their rating of the degree of relational coordination with the endocrinology department, and their rating of using virtual conferences.

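### The 0.05 / 95% interval rule is not reconciled with the 0.0167 test for the three primary clinical outcomes, and the six primary competence outcomes have no multiplicity rule

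*Protocol article*

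**What the plan says.** Protocol article, Outcomes, Clinical outcomes: Bonferroni is used to adjust the p-"values of the three primary clinical outcomes", and a null hypothesis in that family is rejected only if the p-"value is less than 0.0167 (i.e., 0.05/3").

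Protocol article, Statistical analysis plan, opening paragraph: "Statistical significance is expressed in 95% two-sided confidence intervals", and a p-value below "0.05 will indicate statistical significance". The paragraph names no exception and does not refer back to the Outcomes section. The subsection on the month-12 comparison, which follows directly, does not mention the correction.

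Table 2 lists six primary competence and organization measures. General confidence and general skill are separate rows, the latter being "The extent to which the GP is skilled in making decisions on T2D in general". The objectives list has five items, because it merges those two. The running text under Competence and organization outcomes uses the singular: "The primary outcome concerns the competence of the GPs with regards to managing T2D". No multiplicity rule is given for this set.

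Sample and power calculation gives powers of 0.8870, 0.9941 and 0.9848 for the three clinical outcomes and refers to Additional file 5 for the parameters.

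**The concern.** Two sentences set different thresholds for the same three hypotheses. The general one stands under the heading where a reader looks for the decision rule. If p falls between 0.0167 and 0.05, one section says the null is not rejected and the other says the result is significant. The interval level adds a second conflict that does not depend on which threshold wins: a 95% interval corresponds to a 0.05 test, so in that range it excludes no effect while the 0.0167 test does not reject.

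The competence outcomes raise a separate issue. The plan protects one set of outcomes called primary against multiplicity and leaves the other set to the general 0.05 rule without giving a reason. Six tests at 0.05 each give an appreciable chance of at least one false claim on an outcome labelled primary.

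**Working it through.** **Inputs.** Overall alpha 0.05 two-sided, three clinical outcomes and cut-off 0.0167 (Outcomes; Statistical analysis plan). Six competence rows (Table 2), or five items (objectives list). Powers 0.8870, 0.9941 and 0.9848 (Sample and power calculation). Assumptions: the correlations between tests and the alpha behind the powers, neither of which is in the article.

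**1. The plan's own cut-off.** 0.05/3 = 0.016667, which rounds to 0.0167. It reproduces. The matching interval level is 1 − 0.016667 = 98.33%.

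**2. Clinical family.** At 0.05/3 each, the family-wise error is at most 0.05, and 1 − (1 − 0.016667)³ = 0.0492 if independent. Only if the 0.0167 rule were ignored would it be 1 − 0.95³ = 0.143 if independent, or 0.099 at a common correlation of 0.8 (simulation of normal test statistics).

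**3. Competence family at 0.05 each.**

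| Tests | Independent: 1 − 0.95^k | Correlation 0.5 | Correlation 0.8 | Upper bound k × 0.05 |
|---|---|---|---|---|
| 6 | 0.265 | 0.208 | 0.139 | 0.30 |
| 5 | 0.226 | 0.184 | 0.127 | 0.25 |

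The correlated columns are simulated (400,000 runs, normal statistics with a common correlation).

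**4. What the alpha behind the powers would change.** By the normal approximation, noncentrality = z(power) + z(1 − alpha/2), and power at 0.0167 = Φ(noncentrality − 2.394).

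- If the stated powers were computed at 0.05, the noncentralities are 1.211 + 1.960 = 3.171, 2.518 + 1.960 = 4.478 and 2.165 + 1.960 = 4.125. Power at 0.0167 is then Φ(0.777) = 0.781, Φ(2.084) = 0.981 and Φ(1.731) = 0.958. A noncentral t with 28 df (30 practices, two arms) gives 0.765, 0.978 and 0.951.
- If they were computed at 0.0167, they stand as stated.

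**5. How often the disputed range would be hit.** Simulating at the implied effects (independent tests, 400,000 runs), outcome 1 has p between 0.0167 and 0.05 in about 6% of trials if its power was computed at 0.0167, and in about 11% if at 0.05.

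**6. Holm against Bonferroni.** In the same simulation, power for outcome 1 rises from 0.887 to 0.950 if the stated power is at 0.0167, or from 0.781 to 0.884 if it is at 0.05. Holm's ordered cut-offs are 0.05/3 = 0.0167, 0.05/2 = 0.025 and 0.05. Its family-wise error is also at most 0.05, and it rejects whatever Bonferroni rejects.

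**The case against.** The strongest reply is that the specific rule governs the general one. The Outcomes section names the three outcomes and says their nulls are rejected only below 0.0167. The analysis-plan sentence is a default for secondary, survey, baseline and within-arm comparisons. The two can even be read together: a Bonferroni-adjusted p below 0.05 is the same event as a raw p below 0.0167. This stands as the natural reading, and on it the clinical error rate is controlled. It leaves the reader to infer the exception, however, and it does not cure the interval mismatch.

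On competence, the reply is that these outcomes sit at another level, serve a separate objective and are planned for a separate article; that the text speaks of one primary outcome; that indices are foreseen through Cronbach alpha; and that answers from the same GP will be correlated. The correlation argument lowers the figure to about 14–21%, still well above 5%. The rest does not say which row or index is primary, and Table 2 labels all six as primary.

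A reader might go further and infer that the stated powers are wrong or left open. The article does not support that. The alpha may well be given in Additional file 5, which was not available for this review, and the competence outcomes play no part in that calculation. Nor is Bonferroni an error: it is valid, and Holm is an improvement in efficiency.

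**Conclusion.** The point holds in limited form. The threshold and interval level in the Statistical analysis plan section conflict with the Outcomes section for the three primary clinical outcomes. Because the 0.0167 rule naturally governs, this is an unreconciled statement and an interval mismatch, not a loss of error control. The 14.3% figure would arise only if the 0.0167 rule were set aside.

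The six primary competence outcomes are in fact uncorrected. Their family-wise error is 26.5% under independence, which is unlikely for items answered by the same GP, and about 14–21% at assumed correlations of 0.8–0.5.

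The power figures carry no finding. Which alpha they used needs confirming, because outcome 1 would have power of about 0.78 at 0.0167 if 0.8870 was computed at 0.05.

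**What to change.** 1. In the Statistical analysis plan section, limit the 0.05 and 95% interval sentence to outcomes outside the primary families. Secondary outcomes need no relabelling.
2. For the three primary clinical outcomes, choose one of two consistent rules. Either keep Bonferroni, with p < 0.0167 and 98.33% intervals; or, preferably, use Holm at family-wise 0.05, with Holm-adjusted p-values as the decision criterion and any intervals labelled as not matching the stepwise test. Holm cut-offs should not be paired with 98.33% intervals as if they matched: an outcome rejected at a later step with p = 0.02 would have a 98.33% interval that includes no effect.
3. For the competence family, apply Holm across the six rows (first cut-off 0.05/6 = 0.0083), or name one primary outcome or index. Align Table 2, the objectives list and the running text accordingly.
4. As a check, confirm that Additional file 5 used alpha 0.0167. If it used 0.05, restate the powers for the 0.0167 test as about 0.78, 0.98 and 0.96.

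Cost: items 1 and 4, and item 2 if Bonferroni is kept, are clarifications. Adopting Holm, or a rule for the competence family, changes the prespecified testing while recruitment is under way, so it needs a dated amendment before the month-12 results are seen. Holm's small downside is the lack of simple matching intervals. Any rule for the competence family makes each of its claims harder to reach than at 0.05, unless a single outcome or index is named. Sample size and data collection are unaffected.
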